### Allocation concealment

The bachelor physiotherapy degree course regularly allocates students to groups A, B, C or D at the start of every semester. An independent employee of the BFH-SHP carries out the allocation of students by means of a computer-generated random number (Excel, Microsoft). No other member of the institute or the research team has any influence on the randomization process or access to this data. The independent employee keeps the original random number sequences in an inaccessible third location (26). Groups A and B and Groups C and D are together during practical courses to ensure small group sizes. This classification is determined in advance of the start of every semester independent of the investigation by the responsible persons of the educational program. For this planned feasibility study, randomization will be group-based. An independent researcher will assign groups A/B and groups C/D to the G-SS F-SS groups by tossing a coin.

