## Methods

### Study setting

This study is a part of a study project entitled “Retired PhysioTherapists’Tutor Supported Learning” (RePTusule). The aim of the RePTusule project is to evaluate the effects of G-SS by retired physiotherapists on learning outcomes (practical knowledge) as well as the age images of the physiotherapy students and on the physical performance and cognitive capacity of the retired tutors. This study project will start with this feasibility study. The main study will be conducted after finalization of this feasibility study, which was designed as a prospective, single-center, two-armed, randomized-group controlled educational feasibility study, conducted at the BFH-SHP (Figure 1). A feasibility study will be used prior to the main study to depict important parameters required to design the main study (15). This study will enrol undergraduate first semester physiotherapy students from the BFH-SHP and retired physiotherapists in the role of G-SS tutors.

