### Sample size

At the BFH-SHD bachelor’s degree course are always 102 bachelor students enrolled that will be allocated into two groups. We want to recruit five retired physiotherapists. Assuming the intra-cluster correlation coefficient (25) of 0.05 a design effect of 5.25 is given. Sample size is for this study 111.3 (612/5.25).

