### Statistics

Because this study is a feasibility study, testing intervention effects is not a key part of this study design (18). Baseline descriptive statistics will be used to describe G-SS and F-SS group characteristics and to illustrate the feasibility goals. The independent variable will be G-SS. The dependent variable will be the final grades of the MCQs and OSCE. Preliminary group differences at the end of the first semester will be analyzed with the Mann–Whitney-U-Test. The significance level will be set *a priori* to *p* = 0.05. An intention-to-treat analysis will always be the primary analysis of a randomized trial in higher education (17). An ITT will be carried out if physiotherapy students do not adhere to the G-SS protocol.

The findings of the satisfaction and self-efficacy items will be summarized visually in a table and presented as response distributions (number, percentage). Satisfaction analysis will involve the summation satisfaction scale scores, with 0.80 as the proposed threshold for defining usability and acceptability, counting only positive endorsements (4 = agree, 5 = strongly agree). Qualitative data from the semi-structured interview will be analyzed thematically.

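### With one teaching block per arm, the unadjusted Mann–Whitney test of exam grades at 0.05 cannot separate G-SS from the practical class and should be dropped

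*Protocol article*

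**What the plan says.** All references are to the Protocol article.

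- **Allocation concealment.** Students enter four groups, A to D, individually: "An independent employee of the BFH-SHP carries out the allocation of students by means of a computer-generated random number". The groups are then paired for teaching: "Groups A and B and Groups C and D are together during practical courses to ensure small group sizes". The trial allocation acts on those pairs: "For this planned feasibility study, randomization will be group-based", and "An independent researcher will assign groups A/B and groups C/D to the G-SS F-SS groups by tossing a coin".
- **Statistics.** "Preliminary group differences at the end of the first semester will be analyzed with the Mann–Whitney-U-Test", with MCQ and OSCE grades as the dependent variables. "The significance level will be set *a priori* to *p* = 0.05". No cluster term or adjustment is named. The same section says that testing for an intervention effect is not central to the design.
- **Sample size.** "Assuming the intra-cluster correlation coefficient (25) of 0.05", a design effect of 5.25 follows. The sentence before it gives the number of tutors to be recruited, and the one before that says that the 102 enrolled students form two groups.
- **Intervention program.** The G-SS arm is split into five tutor groups of five to six, so 25 to 30 students.

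**The concern.** The randomised unit is the teaching block, and there are two of them, one per arm. A student-level test compares the gap between arms with the spread between students. It takes no account of whatever a semester of shared practical classes adds to everyone in one block. That contribution sits wholly inside the G-SS versus F-SS contrast, and none of the recorded covariates can remove it. The OSCE is the more exposed outcome, because it examines practical skills.

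The Sample size section allows for clustering and the named test does not. At stake is the reading of a p-value below 0.05: practical class alone could produce it, and it could still be taken as support for G-SS when the main study is planned.

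**Working it through.** **1. The plan's own figures.** With design effect = 1 + (m − 1) × ICC, a value of 5.25 at ICC 0.05 needs m = 1 + 4.25/0.05 = 86. That fits neither the tutor groups (m = 5 to 6, design effect 1.20 to 1.25) nor the blocks (m = 51 if all 102 students take part, design effect 3.50). The figures therefore do not show which kind of cluster the 0.05 describes. (The quotient 612/5.25 is 116.6, not the printed 111.3; that is a separate matter.)

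**2. The unit that the test must use.** With blocks as units, 1 versus 1, the smallest two-sided exact Mann–Whitney p is 1.0. With A, B, C and D as units, 2 versus 2, it is 0.33. Only a student-level test can reach 0.05.

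**3. False-positive rate, one block per arm.**

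Inputs:
- no G-SS effect;
- two-sided 0.05 (the protocol does not state sidedness);
- m = 28 per arm, near the middle of the 25 to 30 planned for G-SS, with an F-SS arm of equal size assumed;
- normally distributed scores;
- block ICC treated as unknown, from 0 to 0.05.

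The block effect inflates the variance of the difference, relative to what a student-level test assumes, by V = 1 + m × ICC/(1 − ICC). The true error rate is about 2 × [1 − Φ(1.96/√V)].

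| Block ICC | V | Formula | Simulated Mann–Whitney (20,000 runs) |
|---|---|---|---|
| 0 | 1.00 | 5.0% | 4.9% |
| 0.01 | 1.28 | 8.4% | 7.8% |
| 0.02 | 1.57 | 11.8% | 10.9% |
| 0.05 | 2.47 | 21.3% | 20.3% |

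Worked line for 0.05: V = 1 + 28 × 0.05/0.95 = 2.47; 1.96/√2.47 = 1.246; 2 × [1 − Φ(1.246)] = 21.3%.

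**4. Sensitivity to arm size.** At block ICC 0.05 the simulated rate is 12.7% with 15 per arm (the recruitment minimum of 30, split equally) and 29.8% with 51 per arm (the whole cohort). At ICC 0.01 these become 5.9% and 10.6%.

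**5. Lenient reading.** If A, B, C and D are four independent classes, two per arm, at ICC 0.05 and 28 per arm, the simulated rate is 12.3%.

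**6. Tutor groups only.** Suppose that 0.05 is a tutor-group ICC and there is no block effect. Five groups of six in the G-SS arm have design effect 1 + 5 × 0.05 = 1.25, and the unclustered F-SS arm has 1. Then V = (1.25 + 1)/2 = 1.125 and the error rate is 6.5%. Two simulations gave 6.2% (20,000 runs) and 7.0% (4,000 runs).

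**The case against.** Several points on the other side stand.

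- **Students reach A to D by random number.** The blocks are not pre-existing, selected classes; at the start they differ only by chance. Only what happens after allocation can create a block effect. If shared teaching has no effect (ICC 0), the test keeps its 5% level. Otherwise it tests G-SS and block teaching as one bundle. The protocol does not say that the blocks have different teachers, and Potential confounders rules out mentoring, Moodle exercises and preparatory assignments in that semester. This limits the likely size of a block effect but cannot show that it is zero.
- **The test is not the study.** Statistics calls the differences preliminary, and Aim makes exam scores secondary. Recruitment, time of task, responsiveness, acceptability and tutor recruitment do not use this p-value. This lowers the severity. It does not make the test valid, since an alpha is still fixed in advance.

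Three stronger readings are tempting but not supported.

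- **That the error rate is known to be far above 5%, near 30%.** This needs a block ICC of 0.05 and 51 students per arm. The stated ICC stands next to the tutor count and may belong to tutor groups, and the Intervention program plans 25 to 30 G-SS students.
- **That the test defeats the study's declared purpose because it yields no effect size, SD or ICC.** Study setting says only "A feasibility study will be used prior to the main study to depict important parameters required to design the main study (15"); it names none of these. A Mann–Whitney test does not prevent their being reported, and Data collection methods also mentions parametric methods.
- **That a positive result would be carried forward as proof.** No rule in the protocol makes progression depend on the exam comparison. This is a risk, not a plan.

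**Conclusion.** The design and the named test do not fit together. With one block per arm, block and treatment are completely confounded. Two units leave no degrees of freedom for between-block variation, so no analysis, cluster-adjusted or not, can supply a valid test of G-SS. That conclusion does not depend on any ICC.

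The size of the error does. At about 28 per arm it runs from nominal at a block ICC of 0 to about 20% at 0.05, and is about 6 to 7% if only tutor groups are clustered at 0.05. These figures assume equal arms, a two-sided test and normal scores. The shared-practical argument is more direct for the OSCE than for the MCQ paper.

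This is a should-fix: it affects a secondary, preliminary comparison and leaves the feasibility conclusions intact.

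**What to change.** **Required, in Statistics:**

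- Delete the Mann–Whitney test and its 0.05 threshold for the exam outcomes.
- Report MCQ and OSCE results descriptively by arm: the difference in points, the SD in each arm, and the tutor-group ICC in the G-SS arm. With five tutor groups that ICC will be very imprecise, and the report should say so.
- Add a limitation in these terms: *each arm consists of one teaching block, so the difference between arms cannot be separated from the practical class; any confidence interval omits between-block variance; the comparison is not to be used as evidence that G-SS works.*

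A random effect for tutor group does not replace this statement, because it leaves the block effect untouched and the interval too narrow. The cost is wording only; no data collection changes.

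**Optional design alternative.** Randomise within A/B and again within C/D, so that each practical block contains both arms, and stratify by block. This breaks the confounding with block. It needs a timetable change and brings the arms into closer contact: the Discussion concedes that students talk to each other, but does not accept extra contamination from mixing arms within a class. If whole groups are assigned, there are still only two per arm, and a group-level exact test cannot go below 0.33. It is not part of the required change.

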### Data collection methods

The first collection of data by means of surveys is scheduled for the start of the project (T0). Thereafter, the same surveys will be filled out by the students participating in this planned feasibility study after the fall semester (T1) and after the spring semester (T2). Before-and-after learning effects will be shown in the intervention group and the control group as well as between the groups are presenting using parametric methods. If a retired physical therapist, or a physiotherapy student, does not wish to continue participating in this study, that person will, upon request immediately removed from the study program. The date of discontinuation will be noted and placed in the files or records. The data will be anonymized after the analysis.

### Statistics

Because this study is a feasibility study, testing intervention effects is not a key part of this study design (18). Baseline descriptive statistics will be used to describe G-SS and F-SS group characteristics and to illustrate the feasibility goals. The independent variable will be G-SS. The dependent variable will be the final grades of the MCQs and OSCE. Preliminary group differences at the end of the first semester will be analyzed with the Mann–Whitney-U-Test. The significance level will be set *a priori* to *p* = 0.05. An intention-to-treat analysis will always be the primary analysis of a randomized trial in higher education (17). An ITT will be carried out if physiotherapy students do not adhere to the G-SS protocol.

The findings of the satisfaction and self-efficacy items will be summarized visually in a table and presented as response distributions (number, percentage). Satisfaction analysis will involve the summation satisfaction scale scores, with 0.80 as the proposed threshold for defining usability and acceptability, counting only positive endorsements (4 = agree, 5 = strongly agree). Qualitative data from the semi-structured interview will be analyzed thematically.

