## Abstract

Physiotherapy education in Europe must incorporate self-study units in the curriculum due to the bologna reform. Studies investigating the impact of guided self-study (G-SS) on knowledge and skills in pre-clinical Swiss physiotherapy students are scarce. This study protocol describes a prospective randomized feasibility education study that will primarily examine the feasibility of establishing G-SS using retired physiotherapists as tutors in undergraduate physiotherapy students at the Bern University of Applied Sciences, School of Health Professions. Secondary objective will be to evaluate the effectiveness of six G-SS cycles with retired physiotherapists as tutors on knowledge and skills of pre-clinical undergraduate physiotherapy students. Students of the physiotherapy degree course will be allocated into a G-SS group or control group (CG). G-SS consists of an 8-day cycle. Feasibility outcome are the fidelity of implementation that include exposure dosage and students’ responsiveness, and the degree of acceptability. Success criteria of feasibility are (1) exposure dosage calculated as the number of 90-min presentations that are conducted, and the content of cases and competences and (2) students’ responsiveness, with at least a 83% willingness to participate. Acceptability of intervention from the undergraduate students’ perspective will be evaluated by a questionnaire with open, semi-structured questions (post intervention). This study will provide new information regarding the feasibility of embedding G-SS in the curriculum and about the students’ responsiveness and their acceptability for G-SS.

Study protocol version 1

**Trial registration:** German Register of Clinical Studies (DKRS: DRKS00015518).

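### The Statistics section disclaims effect testing, then names a Mann–Whitney test at 0.05 as its only exam analysis; an estimate with an interval would serve the main study better

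*Protocol article*

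**What the plan says.** All references are to the protocol article.

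- **Purpose (Study setting):** "A feasibility study will be used prior to the main study to depict important parameters required to design the main study". The parameters are not listed.
- **Role of testing (Statistics):** "Because this study is a feasibility study, testing intervention effects is not a key part of this study design".
- **Exam analysis (Statistics):** "The dependent variable will be the final grades of the MCQs and OSCE", then "Preliminary group differences at the end of the first semester will be analyzed with the Mann–Whitney-U-Test" and "The significance level will be set *a priori* to *p* = 0.05". No other comparison of exam results is named there.
- **Descriptive statistics (Statistics):** "Baseline descriptive statistics will be used to describe G-SS and F-SS group characteristics and to illustrate the feasibility goals". Exam scores are not mentioned.
- **Abstract:** "Secondary objective will be to evaluate the effectiveness of six G-SS cycles with retired physiotherapists as tutors".
- **Data collection methods:** in a paragraph on the surveys at T0, T1 and T2, learning effects within and between the arms are to be presented by parametric methods.
- **Outcome measures:** the exams are labelled ordinal, but have point scales with maxima of 87 (MCQ) and 64 (OSCE).
- **Sample size:** an intra-cluster correlation (ICC) of 0.05 is assumed. No power, effect size or SD is stated.

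**The concern.** Two statements in one section pull apart: effect testing is said not to matter much, and then a test with a fixed significance level is the one exam analysis named. The abstract leans further towards testing, and the data collection section points to a different family of methods.

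The stake is what can be carried forward. A U statistic and p-value do not say how many points separate the arms, how uncertain that figure is, or how widely scores vary. A result above 0.05 may be read as showing that guided self-study does not work, and one below 0.05 as showing that it does. A study with no stated power or target effect supports neither reading.

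**Working it through.** **1. The plan's own figures.** There is no stated power to reproduce. The one calculation under Sample size does not supply it: 612/5.25 = 116.6, not the printed 111.3, and neither number is tied to an effect or a power. That arithmetic is a separate matter, and nothing below rests on it.

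**2. Inputs.** Three sizes per arm:
- 15, from the recruitment minimum of 30 (Participants).
- 30, the upper end of five groups of five to six students, i.e. 25 to 30 in the guided arm (Intervention program).
- 51, from 102 enrolled students in two groups (Sample size).

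The true effect of 0.5 SD is my assumption. Results are in SD units because the documents give no SD.

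**3. What the test would deliver.** Simulated two-sided Mann–Whitney test at 0.05, N(0,1) against N(0.5,1), independent students, 20,000 runs per size.

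**4. What estimation would deliver from the same data.**
- 95% half-width of a mean difference, in SD units: t(0.975, 2n − 2) × √(2/n).
  - n = 15: 2.048 × √(2/15) = 0.75
  - n = 30: 2.002 × √(2/30) = 0.52
  - n = 51: 1.984 × √(2/51) = 0.39
- 95% limits of the pooled SD, as multiples of the estimate: √[(2n − 2)/χ²] at the 0.975 and 0.025 quantiles.

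| Per arm | Power at 0.5 SD | Half-width (SD) | SD limits (× estimate) |
|---|---|---|---|
| 15 | 24% | 0.75 | 0.79 to 1.35 |
| 30 | 45% | 0.52 | 0.85 to 1.22 |
| 51 | 68% | 0.39 | 0.88 to 1.16 |

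At 15 and 30 per arm, a non-significant result is more likely than not even with this effect present. At 51 per arm it is not.

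**5. How far those intervals can be trusted.** Under Allocation concealment, a coin toss assigns the combined groups A/B and C/D, so there is one randomised unit per arm and arm is confounded with block. The half-widths above cover student-level variation only. As an illustration, suppose the protocol's ICC of 0.05 applied at block level. The design effect 1 + (n − 1) × 0.05 would be 1.70, 2.45 and 3.50. The half-width 1.96 × √(2 × design effect/n) would become 0.93, 0.79 and 0.73 SD. The study cannot itself check that ICC.

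**6. Could an ICC be estimated?** Between randomised units, no: there is only one per arm. Tutor groups exist only in the guided arm. With five groups of six and an estimate of 0.05, F = 1 + 6 × 0.05/0.95 = 1.316. The F-based 95% interval on 4 and 25 degrees of freedom runs from about −0.11 to 0.63, which is close to uninformative.

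**The case against.** **This is missing detail in a condensed article.** Naming a test does not rule out reporting SDs and intervals, and a fuller document may do so. That is fair, and their absence alone would be no finding. What remains is that the article fixes a test and a level that sit badly with its own statement about testing.

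**The study's purpose does not require exam parameters.** A reader might infer that the plan yields none of the parameters the study exists to supply. The documents do not support that. Study setting lists no parameters, and the primary aim is implementation feasibility. Attendance, acceptability and tutor recruitment are all to be measured, and Participants ties the recruitment rate expressly to the later trial. Exam scores are a secondary aim.

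**The rank test is not the only analysis promised.** The parametric sentence under Data collection methods may cover the exams. It probably concerns the surveys, since no baseline exam is described. If it does cover the exams, it conflicts with the rank test; either way the two sections need reconciling.

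**The exams are labelled ordinal.** A rank method follows from that label, so medians, and a shift estimate if ranks are kept, belong in the report.

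**Misreading is already guarded against.** The differences are called preliminary, which helps. But the abstract's wording on effectiveness works the other way.

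**An ICC should be demanded too.** A reader might infer this from the assumed 0.05. Step 6 shows that the design cannot deliver a useful one, so the main study would still have to assume it.

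**Conclusion.** The point holds as an inconsistency with a nearly costless remedy. Statistics plays down testing, then names only a test at 0.05 for the exams, with no power or effect size behind that level. The abstract and Data collection methods do not agree with it. A p-value alone would not give the effect size or spread that could inform the main study.

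In size: with an assumed 0.5 SD effect, normal scores and independent students, power runs from about 24% (15 per arm) to 68% (51 per arm). A difference could be given to about ±0.75 down to ±0.39 SD, and the SD to within roughly −21/+35% down to −12/+16%. The intervals for the difference are too narrow to the extent that the two blocks differ for reasons other than the intervention. It would go too far to say that a non-significant result is likely at every size, since that fails for the full cohort. The primary feasibility outcomes are untouched.

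**What to change.** 1. In Statistics, make estimation the stated exam analysis. For MCQ and OSCE separately, report per-arm mean and SD, with median and IQR given the ordinal label, and the G-SS minus F-SS difference in points with a 95% CI. If the rank approach is kept, use a Hodges–Lehmann shift with its interval.
2. State beside the interval that it reflects student-level variation only, because arm is confounded with block A/B versus C/D.
3. Label any p-value exploratory and remove the 0.05 decision level.
4. Under Data collection methods, say whether the parametric sentence concerns the surveys or the exams, and align it with Statistics.
5. Reword the abstract's secondary objective as estimating preliminary differences.
6. Do not require an ICC. If a tutor-group ICC is reported, present it as descriptive and very imprecise.

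The cost is wording and a little tabulation of data already being collected. The downside is that there would be no headline significance claim.
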